### Objectives

The overall purpose of this PARITY program is to reinforce protective assets through empowering messaging, promote wellness behaviors, and support Black birthing persons. This pilot trial will provide information on the feasibility, acceptability, and preliminary efficacy of the PARITY intervention among Black pregnant women as well as provide critical information on study design, retention, effect sizes, and outcomes assessment.

The objectives of this study are to (1) explore the feasibility and acceptability of the PARITY intervention; (2) investigate the preliminary efficacy of the PARITY intervention on changes to maternal blood pressure (primary), gestational weight gain, and cesarean birth (secondary) and estimate the effect size of the intervention relative to the control group; and (3) investigate changes to wellness behavioral outcomes (nutrition, physical activity, sleep, and health care adherence) and empowered strengths (self-efficacy, social support, motivation, resilience, problem-solving, and self-regulation) in PARITY intervention participants. With the combination of information, guidance, and support toward leveraging their innate strengths into actionable wellness, we hypothesize that the PARITY program will improve maternal blood pressure, gestational weight gain, and cesarean birth rate in the intervention group compared with the information-only control group. Further, we expect emphasizing individual strengths and building from them while navigating pregnancy-related health care will improve wellness behaviors and empowered strength variables such as adherence to medical care, including appointment adherence.

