### Study Population

Participants will be included in the study based on the following criteria: (1) self-identify as being of Black race, (2) pregnant with gestational age 20 to 28 weeks at enrollment, (3) ability to read and write in the English language, (4) planning to give birth in a health care facility and receive obstetrical care with a health care record, (5) reside within 20 minutes of the identified metropolitan area, (6) 19 to 51 years of age, and (7) own a smartphone with internet access. Participants will be excluded from the study for the following reasons: (1) current involvement in another intervention study, (2) planned pregnancy termination, or (3) inability to provide informed consent.

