### Participant Allocation

Randomization allocation will be guided by the National Cancer Institute Clinical Trial Randomization Tool [32]. This tool generates an allocation scheme using the asymptotic maximal procedure. The following parameter inputs were used in the tool: trial size=60, maximum-tolerated imbalance=3; and arms (ratio 1:1). The output of this randomization allocation tool provides a schedule of randomization.

After signing the informed consent and release of medical record forms, participants will be emailed a secure link to complete the baseline enrollment surveys electronically in REDCap. In addition, each participant will be given the Healthy Pregnancy handout [33], Community Resources handout, and Birth Doula handout, in addition to the standard consent documents. Participants will be randomized according to the randomization schedule based on when they complete the enrollment surveys. Once a participant completes the enrollment surveys, the research coordinator will inform the participant of their group assignment and explain the procedures related to the assigned group.

Individuals randomized to the information control group will be dismissed and informed that they will be contacted by study personnel 6 to 12 weeks post partum to complete the follow-up assessments. Individuals randomized to the intervention group will be contacted by the doula interventionist to schedule their first doula session and be onboarded to the PARITY platform. The interventionist will explain that the participant will receive 3 additional sessions (4 in total) with the doula interventionist in addition to the mobile technology platform where communication can occur with the doula.

During the sessions, the doula interventionist will use the Doula Sessions Manual, which contains a script for each visit. The doula interventionist will track when contact is made with the participant on a form called the Intervention Fidelity Checklist. To ensure the fidelity of the intervention, the doula interventionist’s adherence to the intervention protocol will be measured through an audit of the dates and missed visits on the Intervention Fidelity Checklist and monthly review meetings.

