Maternal blood pressure (primary) at 20 weeks, 36 weeks, birth, and 6 weeks post partum will be measured retrospectively from the medical record at 12 weeks post partum. The data will be analyzed as a continuous variable using the participant’s blood pressure (systolic and diastolic) as well as categorically with the blood pressure classifications of hypertension (>140/90) and severe hypertension (>160/110).Gestational weight gain (secondary), or the amount of weight gained in pounds at 20 weeks, birth, and 6 weeks post partum, will be measured retrospectively from the medical record at 12 weeks post partum.Cesarean birth (secondary) will be assessed from the delivery modality (vaginal, cesarean, or assisted vaginal delivery), measured retrospectively from the medical record at 12 weeks post partum.Perinatal outcomes (exploratory) from birth will be measured retrospectively at 12 weeks post partum via the maternal medical record. The perinatal outcomes that will be measured include preterm delivery; gestational diabetes; birth weight; gestational age at delivery; anesthesia used during labor; labor length; delivery provider type (obstetric physician, family physician, resident physician, or certified nurse midwife); and intrapartum medical diagnoses according to theInternational Classification of Diseases, 10th Revision[34], including hypertensive disorders of pregnancy, intrapartum fever, and postpartum hemorrhage. In addition, the Appearance, Pulse, Grimace response, Activity, and Respiration score of the newborn at birth will be measured as a way to summarize the health of the baby [35].

The following outcome measures will be used to investigate changes to wellness behavioral outcomes and empowered strengths:

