Wellness-related behavioral outcomes:*Nutritional intake* will be measured with the Multifactor Screener, 2000, as used in the Observing Protein and Energy Nutrition Study [36]. This instrument measures approximate intakes of fruits and vegetables and percentage energy from fat and fiber. Respondents will report through a self-administered questionnaire in REDCap how frequently they consume foods in 16 categories and the type of milk consumed. The questionnaire will measure nutrition at baseline and 6 to 12 weeks post partum.*Physical activity* will be measured with the International Physical Activity Questionnaire-Short Form (IPAQ-SF) [37]. The IPAQ-SF consists of 9 items and collects information on the time spent walking, in vigorous and moderate intensity activity, and in sedentary activity over the last 7 days. It is scored by converting the reported time into metabolic equivalent of task (MET) minutes. The MET minutes are then summed to provide an understanding of an individual’s physical activity levels, with low levels being <600 MET minutes per week, moderate activity levels being 600 to 2999 MET minutes per week, and high activity levels being ≥3000 MET minutes per week [37]. It will be self-administered in REDCap and takes approximately 10 minutes to complete. The IPAQ-SF is a reliable (α>.80) and valid instrument [37]. Physical activity will be measured at baseline and 6 to 12 weeks post partum.*Sleep quality* will be measured using the Pittsburgh Sleep Quality Index, a reliable (α>.83) and valid self-report questionnaire that assesses sleep quality over a 1-month time interval [38]. The measure consists of 19 individual items, creating 7 component scores that range from 0 to 3 points. The 7 component scores are summed to produce 1 global score that ranges from 0 to 21 points, with 0 indicating no difficulty and 21 indicating severe difficulty across all areas [38]. Sleep quality will be measured through a self-administered survey, which takes about 15 minutes to complete, in REDCap at baseline and 6 to 12 weeks post partum.*Health care adherence* will be measured by the number of health care appointments attended and missed, which will be logged in the medical record. Health care adherence will be measured throughout the pregnancy continuum and collected at 12 weeks post partum retrospectively via the medical record.Empowered strengths:*Self-efficacy* will be measured using the General Self-Efficacy scale [39] administered in REDCap. The General Self-Efficacy scale is a valid and reliable (α>.75-.90) 1D self-report measure that features a 10-item questionnaire assessing the optimistic self-beliefs of individuals to cope with various challenging demands in life [39]. It takes approximately 5 minutes to complete. The response options are presented along a Likert scale for each item, ranging from 1 (not at all true) to 4 (exactly true). The total score is calculated as the sum of the items, with a higher total score indicating more self-efficacy [39]. Self-efficacy will be measured at baseline and 6 to 12 weeks post partum.*Social support* will be measured using the 10-item Social Provisions Scale [40]. The 10-item Social Provisions Scale is a validated and reliable (α>.80) measure that assesses 5 social provisions: attachment, guidance, social integration, reliable alliance, and reassurance of worth [40]. Each item is rated on a 4-point Likert scale, ranging from 1 (strongly disagree) to 4 (strongly agree), and the individual item scores are then summed to provide a summary score ranging from 10 to 40 [40]. Higher scores indicate higher levels of social support [41]. Social Support will be measured through a self-administered survey, which takes approximately 5 to 10 minutes to complete, in REDCap at baseline and 6 to 12 weeks post partum.*Motivation* will be measured with the Self-Motivation Inventory (SMI) [42]. The SMI is a 40-item, 5-point Likert scale questionnaire that will be self-administered in REDCap and takes about 15 minutes to complete. The SMI is a valid and reliable (α>.91) instrument measuring self-motivation conceptualized as perseverance independent of external support [42]. Motivation will be measured at baseline and 6 to 12 weeks post partum.*Resilience* will be measured using the 10-item Connor-Davidson Resilience Scale [43]. The 10-item Connor-Davidson Resilience Scale is a valid and reliable (α>.85) unidimensional self-reported scale measuring resilience [43]. Respondents will self-report through a survey in REDCap by rating items on a 5-point Likert scale ranging from 0 (not true at all) to 4 (nearly all of the time). Scores range from 0 to 40, with higher scores representing higher resilience [43]. Resilience will be measured at baseline and 6 to 12 weeks post partum through the survey, which takes about 5 minutes to complete.*Problem-solving* will be measured with the Problem-Solving Inventory (PSI) [44]. The PSI is a valid and reliable (α>.86) self-report instrument that measures how well individuals make decisions and their problem-solving abilities [44]. The PSI includes 32 items using a 6-point Likert scale and takes about 10 minutes to complete. The total score of the questionnaire is the sum of all responses, with lower scores representing lower problem-solving abilities [44]. Problem-solving will be measured through a self-administered survey in REDCap at baseline and 6 to 12 weeks post partum.*Self-regulation* will be measured with the Index of Self-Regulation (ISR) [45]. The ISR is a valid and reliable (α>.87) instrument that measures the level of self-regulation for health behavior change in a 9-item scale [45]. Respondents rate items on a 5-point Likert scale, ranging from 1 (strongly disagree) to 6 (strongly agree), with higher sum scores indicating higher levels of self-regulation for a behavior [46]. Self-regulation will be measured at baseline and 6 to 23 weeks post partum in REDCap through the ISR, which takes about 5 to 10 minutes to complete [46].Other variables that will be assessed are demographics, discrimination, and neighborhood:*Demographics:* an investigator-developed form will measure demographic variables, including income, education, ethnicity, insurance, health provider, relationship status, and pregnancy history, at baseline.*Discrimination:* discrimination will be measured using the Everyday Discrimination Scale [47] through a self-administered survey in REDCap. The Everyday Discrimination Scale is a valid and reliable (α>.74) instrument that measures the frequency of chronic and routine unfair treatment in everyday life [47]. Respondents are asked to report how often they experience unfair treatment in their day-to-day life on a 6-point Likert scale ranging from 1 (never) to 6 (almost every day), with total scores ranging from 10 to 60. Higher scores indicate experiencing discrimination frequently and in a variety of situations [47]. Discrimination will be measured at baseline.*Neighborhood:* neighborhood variables will be assessed using the Neighborhood Collective Efficacy-Community Cohesion and Informal Social Control protocol from the Project on Human Development in Chicago Neighborhoods [48]. This valid and reliable (α=.82) measure includes 10 Likert-style questions that assess trust and expectations among neighbors and is used to determine how the neighborhood environment modifies risky behaviors [48]. It will be self-administered as a survey in REDCap and takes about 10 minutes to complete. The measures consist of 2 subscales, Community Cohesion and Informal Social Control, that include 5 Likert-style items, each ranging from 1 (strongly disagree) to 5 (strongly agree). Higher scores indicate greater neighborhood collective efficacy [48]. Neighborhood variables will be measured at baseline.

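### Prior cesarean, probably the strongest baseline predictor of cesarean birth, is neither a stratification factor nor a fixed covariate, which costs the cesarean comparison precision it could keep at little cost

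*Protocol article*

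**What the plan says.** **Eligibility (Study Population).** Women enter if "pregnant with gestational age 20 to 28 weeks at enrollment" and if "planning to give birth in a health care facility and receive obstetrical care with a health care record". The full list of exclusions is "1) current involvement in another intervention study, (2) planned pregnancy termination, or (3) inability to provide informed consent". None of these criteria concerns a prior or planned cesarean.

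**Outcome (Outcome Measures).** "Cesarean birth (secondary) will be assessed from the delivery modality (vaginal, cesarean, or assisted vaginal delivery"). Planned, repeat and intrapartum cesareans are not separated.

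**Hypothesis (Objectives).** The program is expected to "improve maternal blood pressure, gestational weight gain, and cesarean birth rate in the intervention group compared with the information-only control group", and an effect size relative to control is to be estimated.

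**Allocation (Participant Allocation).** The tool inputs are "trial size=60, maximum-tolerated imbalance=3; and arms (ratio 1:1"). One schedule is used in the order in which enrollment surveys are completed, and no strata are named.

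**Covariates (Data Analysis).** Baseline nutrition, physical activity and sleep are fixed covariates. Two rules may add others. One compares arms on each baseline variable and correlates each with outcomes in early participants. The other considers demographic or clinical characteristics that turn out to differ between arms.

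**Baseline data (Outcome Measures).** The demographic form covers "relationship status, and pregnancy history, at baseline". Planned mode of birth is not listed.

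**The concern.** A woman with a prior cesarean is much more likely than others to deliver by cesarean again, whatever her arm. With 30 women per arm and no stratification, the two arms will usually hold different numbers of such women, and each difference carries straight into the cesarean comparison. The three covariates fixed in advance do not capture this.

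Objective 2 wants an effect size to inform a larger trial. If a known, strong predictor is left to a conditional screen, that estimate is noisier than it need be. Its adjustment would also depend on how the arms happened to fall and on outcomes in a small early subset.

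**Working it through.** **The plan's own figures.** There is none for cesarean. The Sample Size section covers blood pressure and weight only. Its detectable differences of 0.81 SD (25 per group) and 0.91 SD (20 per group) reproduce as 0.809 and 0.909 with a noncentral t calculation, but they say nothing about a proportion.

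**Inputs.** From the documents: 60 women, 1:1, hence 30 per arm. Assumed, because the documents give no figures: k = 9, 11 or 15 women with a prior cesarean; cesarean risk 85% in them against 25% in the others, or 75% against 30% with k = 11. All 60 outcomes are taken as observed. A simple random 30/30 split stands in for the asymptotic maximal procedure.

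**Step 1: SD of the chance split.** If X of the k women fall in one arm, the difference in share is (2X − k)/30, with Var(X) = 30 × (k/60) × (1 − k/60) × (30/59). For k = 9 this is 30 × 0.15 × 0.85 × 0.508 = 1.94, so the SD of the share difference is (2/30) × √1.94 = 9.3 points. Multiplying by the risk contrast of 0.60 gives 5.6 points.

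**Step 2: total standard error.** The overall rate is p = (k/60) × risk in prior-cesarean women + (1 − k/60) × risk in the others, and SE = √(2p(1 − p)/30). For k = 9, p = 0.15 × 0.85 + 0.85 × 0.25 = 0.34 and SE = √(2 × 0.34 × 0.66/30) = 12.2 points.

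**Step 3: share of variance.** This is (split SD)²/SE². The last column is √(SE² − SD²), the SE left if that part were removed by adjustment on the risk-difference scale.

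| k | Risks | p | Split SD | Total SE | Share of variance | Remaining SE |
|---|---|---|---|---|---|---|
| 9 | 85% v 25% | 34.0% | 5.6 | 12.2 | 31.1/149.6 = 21% | 10.9 |
| 11 | 85% v 25% | 36.0% | 6.0 | 12.4 | 36.5/153.6 = 24% | 10.8 |
| 15 | 85% v 25% | 40.0% | 6.8 | 12.6 | 45.8/160.0 = 29% | 10.7 |
| 11 | 75% v 30% | 38.3% | 4.5 | 12.5 | 20.6/157.5 = 13% | 11.7 |

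(SDs and SEs in percentage points, variances in points squared.)

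**Step 4: scale against an effect.** Suppose the program cuts cesarean by 30% in relative terms among women without a prior cesarean and does nothing for the rest. From a 25% risk that is 7.5 points in those women. Over all women it is 0.85 × 7.5 = 6.4 points (k = 9) or 0.75 × 7.5 = 5.6 points (k = 15). The matching split SDs are 5.6 and 6.8, so a one-SD split is about as large as such an effect. With 30 per arm and control rates of 25% to 40%, the difference detectable at 80% power is 24 to 31 points, far above the split SD.

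**Step 5: restricting the outcome instead.** Dropping all prior-cesarean women leaves 51 (k = 9) or 45 (k = 15). The SE is √(2 × 0.25 × 0.75/25.5) = 12.1 or √(2 × 0.25 × 0.75/22.5) = 12.9 points; with 75% v 30% and k = 11 it is √(2 × 0.30 × 0.70/24.5) = 13.1. Precision does not improve. If the program halved cesareans in the remaining women and had no effect in the others, power would rise only from about 12–17% to 19–25%.

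**The case against.** **The plan already has a route to adjustment.** Data Analysis screens each baseline variable for imbalance and for correlation with each outcome, and pregnancy history is a baseline variable. A predictor as strong as assumed here might well be picked up. That stands in part: the plan does not simply ignore the issue. But the screen is conditional, and it relies on outcomes in early participants, where cesarean correlations will be imprecise. The value of adjusting for a strong predictor does not depend on whether the arms differ visibly on it. Choosing it after looking at both also makes the reported effect depend on the data.

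**Chance imbalance is ordinary sampling error.** This is right. Randomization keeps the comparison unbiased, and the confidence interval already includes the split. A reader might infer that such splits could swamp any program effect. The documents do not support that: the split is a minority of the variance even under the assumed inputs, and the main limit is 30 women per arm.

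**Prior is not the same as planned.** A reader might also infer that these women cannot respond to the program. Under the assumed risks, 15% to 25% of women with a prior cesarean deliver vaginally, and the program covers raising questions with providers and navigating care. An absence of effect in them is therefore not shown.

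**Redefining the outcome has its own risk.** Records are extracted at about 12 weeks post partum by staff who are not blinded. Classifying a cesarean then as planned before randomization would settle the analysis set when arm and birth mode can be known. This stands, and is why the all-women rate should remain the outcome.

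**Conclusion.** The point holds as one of avoidable imprecision in a secondary outcome of a pilot. Women with a prior or planned cesarean are eligible and counted, and neither the allocation nor the fixed covariates address it. Under the stated assumptions, prior cesarean accounts for about 13% to 29% of the variance of the between-arm difference.

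The corresponding share of individual outcome variance is (k/60)(1 − k/60) × contrast²/[p(1 − p)], which runs from 0.150 × 0.2025/0.236 = 0.128 (75% v 30%, k = 11) to 0.1875 × 0.36/0.24 = 0.281 (85% v 25%, k = 15). Since 1/(1 − 0.128) = 1.15 and 1/(1 − 0.281) = 1.39, adjustment on the risk-difference scale would be worth roughly 15% to 39% more participants.

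Every one of these sizes rests on assumed prevalence and risks; a smaller share of prior cesareans or a weaker contrast shrinks them. Adjustment would not make the cesarean comparison well powered. Nor would it cover women whose cesarean is planned for another reason, since planned mode of birth is not a listed baseline item.

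**What to change.** Leave eligibility, the randomization schedule and the all-women cesarean rate as they are. In Data Analysis, name prior cesarean, taken from the baseline pregnancy-history form, as a fixed covariate or analysis stratum for the cesarean comparison, used whether or not the arms differ on it. Report the resulting difference with its confidence interval. Cesarean among women without a prior cesarean, classified from the baseline form alone, may be added as a supportive analysis.

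The cost is one extra model term in a sample of 60, with no new visits or participants. The fix assumes that the pregnancy-history form records prior cesarean, which the article does not spell out and the sponsor should confirm.

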
### Data Analysis

Participants will be described using standard summary statistics and distribution plots of measured variables at each point in time. We will estimate the standardized magnitude of each baseline difference and the correlation between each baseline variable and each outcome of interest in the interim and primary end point of early participants to objectively determine baseline variables that will be needed to estimate the unbiased effect of PARITY on each outcome. A shared random component generalized linear mixed model (GLMM) will be used to simultaneously describe and compare the effects of PARITY on clinical outcomes, wellness-related behavioral outcomes, and empowered strength outcomes over the measurement periods [49]. A shared random component model will account for the correlation within participants on any 1 measure and the correlation between measures on the same participant at the same time point. The effect of time will be treated as a fixed effect. The time-by-group interaction will be tested; if the interaction *P* value is >.10, it will be dropped from the model. Baseline nutrition, physical activity, and sleep measures will be used as covariates to control for potential differences in the groups and to avoid detecting spurious time-by-treatment interactions due to the random assignment of participants to groups. Demographic or clinical characteristics exhibiting differences between groups at baseline will be investigated as potential covariates in the models. For significant effects, preplanned post hoc contrasts will be computed, and *P* values will be adjusted using the Holm method to maintain comparison-wise error at or <.05 [50]. Unless otherwise specified, the significance level for all tests will be.05.

Missing outcome data caused by loss of follow-up are possibly related to the participant’s unobserved outcome measures (nonignorable missingness). The GLMM provides unbiased estimates under missing completely at random and missing at random mechanisms. The data will be reanalyzed using a pattern-mixture model (PMM) to allow for different coefficient changes based on dropout patterns [51]. GLMM and PMM marginal treatment effects will be compared. If the marginal treatment effects differ by >10%, the missingness mechanism will be assumed not at random, and the PMM model marginal estimates will be used to draw conclusions.

Interview data will be analyzed using a thematic analysis approach [52]. The audio recordings will be transcribed verbatim, and the accuracy of the transcripts will be verified by a separate team member who will cross-reference the transcriptions with the audio recordings. Transcripts from interviews will be independently coded in a word processing software by 2 members of the research team. Coding will be completed using an inductive approach to look for specific to more broad patterns across the interview data collected [53]. This will allow for themes and patterns to emerge directly from the data. A list of codes will be recorded and described in a codebook along with the definitions and descriptions of codes and representative quotes from the data so that codes have distinct boundaries. After the data are independently coded, the 2 researchers will discuss the codebook and resolve any discrepancies. The codebook will also help to assess interrater reliability among team members in applying codes to the data [54]. Codes will then be categorized into potential themes by clustering similar codes from participant responses. Audio recordings will be destroyed after transcription has been confirmed. Transcriptions will be destroyed at the end of the study.

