### Outcomes

The feasibility of a full trial will be monitored throughout the study (eg, the randomization, recruitment, and retention of participants; data collection; and adherence). Additional data will be collected only on intervention participants. These include data on engagement with the PARITY intervention based on the number of hyperlinks clicked, time engaged in the content, and the number of doula sessions completed throughout the 12 weeks. A total of 10 to 15 intervention participants will be asked to complete a qualitative interview to discuss their experiences with the intervention and the acceptability of the technology component, doula component, and strength messaging component at 12 weeks post partum.

Clinical maternal outcomes (maternal blood pressure, gestational weight gain, delivery modality, and exploratory perinatal outcomes) will be measured at 20 weeks, 36 weeks, birth, and 6 weeks post partum and will be collected from the medical record. At baseline (20-28 weeks’ gestation), demographics, discrimination, and neighborhood variables will be assessed using self-report questionnaires administered via REDCap (Research Electronic Data Capture; version 14.3.11) [30,31]. At baseline and 6 to 12 weeks post partum, wellness-related behavior outcomes (nutritional intake, physical activity, and sleep quality) and empowered strengths (self-efficacy, social support, problem-solving, motivation, resilience, and self-regulation) will be measured using web-based self-report questionnaires in REDCap. In addition, health care adherence (the number of prenatal appointments) will be evaluated retrospectively using medical records.

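### Dropping the time-by-group term when P>.10 can leave a group effect averaged with a pre-randomisation value; if baseline is a response, it is diluted by 25–50% in trials where the term is dropped

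*Protocol article*

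**What the plan says.** In the Protocol article, Data Analysis, one shared-random-component GLMM is to describe and "compare the effects of PARITY on clinical outcomes, wellness-related behavioral outcomes, and empowered strength outcomes over the measurement periods". On time, the section says "The effect of time will be treated as a fixed effect". It then gives the reduction rule: "The time-by-group interaction will be tested; if the interaction *P* value is >.10, it will be dropped from the model". The next sentence names the prespecified covariates: "Baseline nutrition, physical activity, and sleep measures will be used as covariates to control for potential differences in the groups". Baseline blood pressure, baseline weight and the baseline strengths scores are not on that list.

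Outcome Measures lists "Maternal blood pressure (primary) at 20 weeks, 36 weeks, birth, and 6 weeks post partum" and, for weight, "the amount of weight gained in pounds at 20 weeks, birth, and 6 weeks post partum". The Outcomes section gives the wellness and empowered-strength questionnaires two occasions only: baseline and 6 to 12 weeks post partum. Study Population puts enrolment at 20 to 28 weeks, and Participant Allocation randomises after the enrolment surveys are complete. The first listed value of each repeated outcome is therefore at or before enrolment and cannot carry a treatment effect.

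**The concern.** When the pre-randomisation value is one of the responses, the arms are equal in expectation at that occasion, and the treatment effect is the time-by-group term. Dropping that term leaves a group coefficient that is a weighted average of the arm differences at every occasion, including the one where the true difference is zero. Chance imbalance at baseline is averaged in too.

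The rule also makes the estimand depend on a P value. One outcome could be reported as a post-baseline contrast and another as a baseline-diluted average. It gives two routes to significance: the interaction or, after dropping it, the group term.

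This matters because the Objectives section asks the pilot to estimate the effect size relative to control, and the Results section says the pilot will inform a larger trial. Required sample size scales with 1/d². An effect shrunk to 0.75d inflates it by 1/0.75² ≈ 1.8, and one shrunk to 0.5d by 1/0.5² = 4.

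**Working it through.** **The plan's own figure.** The sample size section gives 80% power for 0.81 SD with 25 per group, and for 0.91 SD with 20 per group (two-sided t test, alpha .05). With the noncentral t:
- 25 per group: noncentrality 0.81 × √(25/2) = 2.86, 48 df, power 80.1%.
- 20 per group: noncentrality 0.91 × √(20/2) = 2.88, 38 df, power 80.1%.

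Both reproduce. The problem lies in the analysis rule, not in these figures.

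**Inputs.** n = 25 per arm and d = 0.81 SD come from the sample size section. A smaller effect of 0.50 SD is added for illustration. T, the number of occasions including baseline, is 4 (blood pressure), 3 (weight) and 2 (strengths scales). Within-person correlation ρ is not given, so 0.3, 0.5 and 0.7 are assumed. The true effect is taken as constant after baseline, m = (0, d, …, d), with complete data and one outcome at a time.

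**Coefficient left after dropping.** In the additive group + time model the generalised least-squares group coefficient is (1′V⁻¹m)/(1′V⁻¹1). Under compound symmetry this is d(T−1)/T:
- T = 4: 0.75d, a 25% dilution. True 0.81 becomes 0.61; true 0.50 becomes 0.375.
- T = 3: 0.667d, a 33% dilution.
- T = 2: 0.50d, a 50% dilution. True 0.81 becomes 0.41; true 0.50 becomes 0.25.

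Under AR(1) with ρ from 0.3 to 0.8 the dilution is 29–42% (T = 4), 37–45% (T = 3) and 50% (T = 2). In simulations at 0.50 SD, the mean estimate in trials that dropped the term was about 0.36–0.39 SD (four times) and 0.24–0.26 SD (two times).

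**How often the term is dropped.** The interaction F test at .10 has noncentrality (n/2) × d² × ((T−1)/T)/(1−ρ). For T = 4, d = 0.81, ρ = 0.5: 12.5 × 0.656 × 0.75/0.5 = 12.3 on 3 and 144 df, giving a 9% chance of dropping. Across the assumed correlations:

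| d | T | ρ = 0.3 | ρ = 0.5 | ρ = 0.7 |
|---|---|---|---|---|
| 0.81 | 4 | 21% | 9% | 1% |
| 0.81 | 3 | 20% | 9% | 1% |
| 0.81 | 2 | 23% | 12% | 2% |
| 0.50 | 4 | 58% | 47% | 26% |
| 0.50 | 3 | 57% | 45% | 25% |
| 0.50 | 2 | 57% | 46% | 27% |

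Simulation puts the lowest value at 0.50 SD at about 24%.

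**Average over all trials.** Suppose the post-baseline mean difference is reported whenever the term is kept (an assumption; the result depends on it). The mean reported effect for a true 0.81 is then 0.78–0.81 (four times) and 0.76–0.81 (two times). For a true 0.50 it is 0.46–0.48 and 0.42–0.47. Allowing for simulation error, that is shrinkage of about 0–9% for blood pressure and up to (0.50 − 0.42)/0.50 = 16% for two-occasion scales.

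**Error rate.** Under the null, the interaction gives P<.05 in 5% of trials and is dropped in 90%. The group test then rejects in 5% of those: 0.05 + 0.90 × 0.05 = 9.5%. Simulation gives about 9–10%.

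**Power at 0.50 SD.** With four times, power is 57–72% under the rule against 74–88% for a baseline-adjusted comparison of the post-randomisation mean. With two times and ρ = 0.5 it is 49% against 52%, almost no loss.

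**The case against.** The strongest objection is to the premise. The article never says outright that the pre-randomisation value is a response, and its phrase about measurement periods is ambiguous. The same paragraph proposes to relate baseline variables to later outcomes in early participants in order to choose adjustment variables, so baseline blood pressure could enter as a covariate. The rule is also written for a joint model that includes blood pressure, which has three post-baseline times, so an interaction can exist without any baseline response.

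This stands in part: baseline as a response is an inference. It remains the better reading. A two-occasion scale can have its own time-by-group term only if baseline is a response. The stated wish to guard against chance time-by-treatment interactions points the same way. No common-baseline or post-randomisation-only model is described, and selection of baseline blood pressure as a covariate is not assured.

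The second objection is about size, and it stands. A reader might infer that the reported effect will simply be 25–50% too small. The documents do not support that: the dilution applies only in trials where the term is dropped, which is the minority at the plan's own 0.81 SD.

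Third, this is a 60-person pilot whose first objective is feasibility and acceptability. Summary statistics at each time point are planned, so unadjusted post-baseline differences will still be available for planning the larger trial. That lowers the severity. It does not justify a rule that lets a P value choose the reported effect.

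**Conclusion.** The point holds in conditional form. If baseline is among the responses, following the written rule gives a diluted effect whenever the interaction is dropped: 25% for blood pressure, 33% for weight and 50% for the strengths scales under compound symmetry, and more under AR(1) for the first two. Dropping is uncommon to moderately common at the planned effect and happens in roughly a quarter to over half of trials at 0.50 SD. The average bias over all trials is therefore modest. The near-doubled null rejection rate and the power loss with four times add to the case.

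These sizes rest on an assumed correlation of 0.3–0.7, a constant post-baseline effect, complete data and single-outcome models rather than the joint GLMM. Cesarean birth and appointment counts are unaffected because they are not repeated measures. Nutrition, physical activity and sleep are unaffected if their baselines serve only as covariates. If every outcome's baseline is a covariate and only post-randomisation values are responses, a constant effect is recovered without dilution. This should be fixed before analysis; it does not invalidate the trial.

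**What to change.** Delete the P>.10 drop rule. State how each outcome's baseline enters the model: either a longitudinal model with a baseline mean common to both arms, or post-randomisation values as responses with the outcome's own baseline as covariate. Name in advance the between-arm contrast to be reported for each repeated outcome, either at a stated post-randomisation time or as the average over those times. Report it with its 95% CI whatever the interaction P value. The interaction can still be shown descriptively.

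The cost is a wording change in the analysis section. It needs no new data, visits or participants.
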